## Abstract

**Background:**

After treatment completion, breast cancer (BC) survivors frequently experience residual symptoms of pain, fatigue, high levels of psychological stress, anxiety, depression, fear of recurrence, and metastasis. Post-treatment stress, in particular, can adversely affect health-related quality of life, which, in turn, induces onset or recurrence of chronic diseases. Effective interventions that target these psychological symptoms and their physiological consequences are needed, especially for economically disadvantaged patients. However, in China, few evidence-based intervention strategies have been established among BC survivors. This study will formally adapt, develop, and evaluate an intensive mindfulness-based stress reduction (MBSR) intervention protocol to improve mental health, quality of life, and compliance with medication among Chinese BC survivors.

**Methods:**

A randomized, waitlist-controlled clinical trial will be conducted. Based on our power calculation, 418 BC survivors will be recruited from 10 low-income communities in Shanghai. All subjects will be randomly assigned either to the MBSR program or to a waitlisted usual care regimen that will offer the MBSR program after the completion of the other trial arm (after 6 months follow-up). Our 8-week MBSR intervention program will provide systematic training to promote stress reduction by self-regulating arousal to stress. Assessments will be made at baseline, 4 weeks (in the middle of the first MBSR intervention), 8 weeks (at the end of the first MBSR intervention), 6 months, and 12 months, and will include measures of psychological symptoms (depression, anxiety, and perceived stress), quality of life, and medication adherence. The expected outcome will be the improvement in psychological symptoms, quality of life, and medication compliance in the MBSR intervention group.

**Discussion:**

This study will help develop an affordable, self-care psychological intervention protocol to help Chinese BC survivors improve their quality of life, and could be helpful in further developing affordable disease management plans for patients of other chronic diseases.

**Trial registration:**

ChiCTR-IOR-14005390 (10/27/2014)

## Background

Breast cancer (BC) is a major public health challenge, accounting for 16.8 % of all cancer cases in China among women aged above 18 years [1]. With a 5-year all-stage survival rate of 85 % [1], BC prevalence in China has continued to increase over the past two decades, with a decrease in the age of incidence [2]. Even though the survival rate for stage I or II BC patients has improved, the emotional impact of a cancer diagnosis and the side effects of cancer treatment (e.g., body incompleteness after mastectomy, hair loss after chemotherapy) have elevated the stress levels of many BC survivors [3]. Evidence demonstrates that almost 60 % of BC patients report high levels of anxiety, while 25.6–58 % report living with depression [4, 5]. This prevalence level is much higher than that of the general population, and is even higher than that of patients of other cancer types. Emotional distress adversely affects these women’s quality of life (QOL) and this may persist beyond treatment [6].

After women have completed main treatments (such as chemotherapy and radiotherapy) for BC, they have to face the stage of “watchful waiting”, a stressful period when the physician seems to be “doing nothing”. Therefore, survivors continue to report remaining physical symptoms of pain, fatigue, and sleep dysfunction, high levels of psychological stress, anxiety, depression, fear of recurrence and metastasis, and impaired QOL [7, 8]. This psychological impact adversely affects neuroendocrine stress response systems, which may lead to immunological disturbance [9] and may even contribute to the recurrence or progression of the disease [10]. Further, these mental health challenges may lower the social functioning of the patient or affect her compliance with further treatments (like oral drug therapy) [11]. It is thus no surprise that psychosocial variables are key predictors of both short-term and long-term QOL [12, 13]. Consequently, psychosocial interventions need to be used as an important supportive therapy for minimizing mortality and morbidity among BC survivors. Evidence shows that the post-treatment stage seems to be an ideal period to introduce stress reduction interventions [14]. However, only very limited research and treatment regimens have been developed to minimize this high degree of morbidity during the difficult transitional period of post-treatment survivorship.

In China, to the best of our knowledge, there have been relatively few psychosocial interventions for cancer patients or survivors, with a particular scarcity of effective stress reduction interventions. Wan (2008) [15] analyzed the impact of a psychological intervention on stress by measuring cortisol and interleukin-2 in perioperative BC patients. Li [16] reported the effects of psychological interventions on illness uncertainty and coping styles of BC patients undergoing chemotherapy. Nevertheless, these intervention studies have mainly been designed to decrease stress and improve physical and psychological functioning among BC patients while on treatment or at diagnosis. Furthermore, the psychological intervention programs used in these studies are based on usual care, including health education and language guidance for patients. Since such interventions have not been developed into established protocols, the applicability to psychological stress relief effect is limited, and there is no evidence that the intervention effect is sustainable. These studies have been carried out simply as pilot studies without follow-up trials, and thus their treatment procedures have not been fully developed into policies or protocols. Further, survivors from low-income households may not be able to afford expensive psychosocial therapies or intervention programs in psychiatric hospitals, even if they need the care. Zhou et al. [17] analyzed the average outpatient expenses for depressive patients in Shanghai, showing that the average outpatient expense was 264 RMB per visit in 2005, 71 % higher than in 2002, after adjusting for consumer price index. Thus, it is necessary to develop an affordable, self-care intervention protocol for mental health in BC survivors, especially for economically disadvantaged patients who still need to work to pay for their follow-up treatments and monitoring.

Mindfulness-based stress reduction (MBSR) uses meditation to cultivate conscious awareness (i.e., mindfulness) of one’s experience in a non-judgmental or accepting manner [18]. MBSR includes both didactic and experiential elements that focus on mindfulness-based meditative practices [19]. It is premised on the belief that bringing greater awareness to actual experience in the “here and now” encourages a disengagement from self-related thoughts (e.g., rumination) and emotions (e.g., anxiety) that can have a detrimental effect on well-being [20]. Generally, a MBSR intervention program is 6 or 8 weeks long and includes weekly 2-hour group sessions where participants receive systematic training to promote stress reduction by self-regulating mindfulness practices such as sitting meditation, body scan, and yoga, among others. Participants are also taught informal practices which emphasize bringing mindfulness practice into day-to-day life, and require home practice of 15–30 minutes per day.

MBSR’s effectiveness in reducing stress has been proven in different populations, including patients with chronic pain [21], anxiety [22, 23], and depression [24]. The effectiveness of MBSR in mental health has also been documented for women with early-stage BC [25]. Henderson et al. [26] tested the effectiveness of a MBSR program compared with a nutrition education intervention and usual care in women with newly diagnosed early-stage BC undergoing radiotherapy, and confirmed its efficacy in facilitating psychosocial adjustment in these women. Witek-Janusek et al. [27] showed that an MBSR program was feasible for women recently diagnosed with early stage BC and provided preliminary evidence of its beneficial effects on immune function, QOL, and coping effectiveness. However, as a lifestyle-oriented, non-pharmacological intervention, with its long-term self-sustainable feature [23], MBSR has only been used in China for populations with no clinical indications (like nurses, students) to reduce stress [28].

Many MBSR studies among cancer survivors have at least one of the following limitations: small sample size (less than 100), short follow-up (just after intervention program ends), or a high ratio of Caucasian participants. Moreover, no studies to date have explored MBSR’s possible impact of enhancing patient compliance with treatment guidelines, even though its effect in improving working memory suggests that MBSR might help patients to better maintain medication and hospital follow-up schedules [29]. In this proposed study, we plan to use MBSR to improve the mental health and treatment compliance among BC survivors. Our proposed MBSR intervention will fill the research gap by exploring its impact on adjuvant therapy compliance in addition to mental health outcomes.

## Study objectives

### Overall goal of the project

This proposed study attempts to improve BC survivors’ mental health and QOL, especially those in low-income families to reduce inequity in mental health care.

This project has two phases: a pilot study and the main study.

### Objectives of the pilot study

Modify the MBSR intervention program to suit the Chinese context.Revise the measuring instruments to suit the Chinese context and the intended subjects (women with low income).Assess the feasibility of the proposed procedures.

### Objectives of the main study

Evaluate the effect of MBSR intervention program in BC survivors.Develop a special affordable, non-medical, self-care psychosocial intervention protocol for Chinese BC survivors.Develop policy recommendations for mental health among BC survivors.

## Theoretical model and hypotheses

### Theoretical model

The psychosomatic response mechanism in BC survivors is graphically presented in Fig. 1. As discussed above, cancer diagnosis and treatment would adversely affect BC survivors’ stress reaction, but the stress level may be influenced by intermediate variables (like survivors’ awareness to disease, coping strategy, social support, and personality). For the various types and intensities of these intermediate variables, different BC survivors would have different psychosomatic responses. BC survivors frequently experience high levels of psychological stress, which is often accompanied by dysregulated neuroendocrine function and immunological disturbance. These impairments are associated with increased tumor initiation, primary tumor growth, and tumor metastasis, which is the primary cause of death from BC [30–32].

**Fig. 1 Fig1:**
[figure not shown]
A theoretical model of breast cancer survivors’ psychosomatic response mechanism

MBSR is a mind-body intervention that shows promise for the management of stress associated with cancer. We hope to show that MBSR reduces neuroendocrine stress activation and improves the immune function of BC survivors after the vulnerable periods of cancer diagnosis and treatment [33, 34]. This would in turn further contribute to improvement of QOL among BC survivors, which would promote psychosomatic balance (Fig. 2).

**Fig. 2 Fig2:**
[figure not shown]
A model of psychological intervention’s mechanism

### Primary hypotheses

Participants in MBSR would show improvements in mental health, QOL, and medication treatment compliance, relative to control subjects. We predict that MBSR would help reduce psychological distress and increase patients’ ability to monitor negative cognitions and thereby decrease stress.The levels of mindfulness would increase over the course of the 8-week MBSR program, serving as a mediator to positive changes in mental health, QOL, and medication treatment compliance.

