### Secondary hypotheses

MBSR would be an intervention modal with a long-term effect. We predict that at 1-year follow-up, the MBSR group would still show improvements in mental health, QOL, and medication treatment compliance, compared with its baseline levels.

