#### Implementation

Following completion of their hospital treatment, BC survivors return home. As part of the newly launched cancer registry system, each community health service center (CHSC) in Shanghai collects BC survivors’ detail information in order to ensure follow-up and to analyze mortality and morbidity rates. Based on the patient lists from CHSC, we will contact these BC survivors directly to recruit potential participants. All participants who are willing to attend this trial will be requested to submit a signed informed consent. After that, all participants who provide an informed consent will then complete a baseline questionnaire for psychometric assessment (Time 0), with the help from investigators. Information about demographic background and health status will also be collected and later verified by a review of hospital charts.

The immediate intervention group will start the program within 2 weeks of randomization. Two certified MBSR psychotherapists will be hired to implement a standard MBSR intervention. Members of the research team will attend each MBSR session to ensure that intervention standards are met.

All subjects will be reassessed after the intervention group completes half of the program (4 weeks into the intervention, Time 1), 8 weeks later (Time 2), and at 6 (Time 3) and 12 months (Time 4) from the beginning of the intervention. Participants in the control group will be given the opportunity to complete the MBSR program after 6 months follow-up. Eight investigators will be in charge of these follow-ups by telephone.

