### Statistical methods

We will compare the outcome variables (SDS, SAS, MAAS, Quality of Life Index, and MMAS) between the two groups using the χ^2^ test for categorical variables and Student t or Wilcoxon tests for continuous variables. Analysis of covariance (ANCOVA) will be conducted to assess whether MBSR is related to changes between baseline and after 8 weeks of intervention in relation to psychological status, QOL, and compliance behaviors.We will use a structural equation model [45] to examine the intervening role of mindfulness enhancement on improving mental health, QOL, and compliance with medical treatment. Mediation analysis, as implemented in MPlus 7.11, will be used to analyze the causal pathway from MBSR intervention to health outcomes through mindfulness enhancement.We will use a random-effects repeated measures analysis [46] to examine the impact of MBSR intervention on health outcomes, compliance behavior, adjusting for confounding variables (age, education, household income, occupation, previous cancer history, and household registration status: Shanghai vs. non-Shanghai). The repeated measure analysis approach accounts for the same individual’s different outcome measures across different points in time without assuming either linear or curvilinear growth pattern. Cronbach alpha’s will be computed to determine the internal consistency of our outcome measures. Using this approach (as implemented by the PROC MIXED and PROC GLIMMIX modules in SAS 9.0), we have published an article analyzing a famous randomized controlled trial of lung cancer screening, which shows a behavioral differential between the two trial arms [47].

The relationship between methods used for each hypothesis is shown in Table 1.

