## Discussion

The largest threat to our study’s internal validity is the possible “contamination effect” (or spillover effect) between the two trial arms. As our participants will be recruited from 10 low-income communities from two of Shanghai’s poorer districts, it is possible that some of these participants know each other and may hold discussions regarding the MBSR treatment. The contamination effect could compromise measurable differences between the two trial arms and bias the intervention result toward the null hypothesis. However, as MBSR takes a substantial amount of exercise to achieve measurable results in mental health, it is unlikely that contamination alone could diminish the difference between those who attend the class and those who only hear about the practice. Plus, we will communicate to the waitlist control group in written materials to make sure that they start MBSR practice only when they receive the intervention.

**Table 1 Tab1:** Summary of methods used for each hypothesis

Objective (main study)	Hypothesis	Method
Objective 1	Primary Hypothesis 1: Improvement in mental health, quality of life, and medication treatment compliance in mindfulness-based stress reduction (MBSR) group	Method 1: Bivariate analyses and ANCOVA
	Primary Hypothesis 2: Relation between MBSR and improvement	Method 2: Mediation analysis in structural equation modeling
Objective 2	Secondary Hypothesis: Long-term improvement of MBSR	Method 3: Repeated measures analysis
Objectives 3 and 4	N.A.	Expert consultation

There is also the possible threat to internal validity through high attrition among participants. Attending an 8-week course is not a trivial matter for young working women, and thus it is possible that those who do not experience an immediate gain in mental health are more likely to quit. This possible pattern of selective attrition could lead to overestimation of intervention impact, as most of those who stay until the end of the intervention are more likely to experience MBSR benefits. We believe, however, that our financial incentive for participants should be sufficient for most BC survivors to complete the course, so long as we appropriately program the timing of our financial incentive (e.g., payment will be given out at each session, instead of being given out in a lump sum at the beginning).

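### Primary hypothesis 2 claims a causal pathway through mindfulness, but nothing stated protects the mindfulness-to-outcome link, and on the natural reading both are measured over the same 8 weeks

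*Protocol article*

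**What the plan says.** The protocol article makes mediation one of its two primary hypotheses: "The levels of mindfulness would increase over the course of the 8-week MBSR program, serving as a mediator to positive changes" (Primary hypotheses).

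Under Statistical methods, a structural equation model is to be used "to examine the intervening role of mindfulness enhancement on improving mental health, QOL, and compliance with medical treatment", and then: "Mediation analysis, as implemented in MPlus 7.11, will be used to analyze the causal pathway from MBSR intervention to health outcomes through mindfulness enhancement". Table 1 assigns this hypothesis to "Method 2: Mediation analysis in structural equation modeling". None of these places names a visit for the mediator or the outcome.

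One outcome window is given for the primary hypotheses. It belongs to the ANCOVA, which is to assess "whether MBSR is related to changes between baseline and after 8 weeks of intervention in relation to psychological status"; Table 1 links the ANCOVA to primary hypothesis 1. The later prediction, "We predict that at 1-year follow-up, the MBSR group would still show improvements", is a secondary hypothesis, and Table 1 assigns it to repeated measures.

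The adjustment for age, education, household income, occupation, cancer history and household registration is stated in the sentence on the random-effects repeated-measures analysis only.

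On timing, Implementation says "All subjects will be reassessed after the intervention group completes half of the program (4 weeks into the intervention, Time 1", with further assessments at 8 weeks, 6 months and 12 months, by telephone. The waitlist arm is offered MBSR after the 6-month follow-up. MAAS is listed among the outcome variables, but no visit schedule is given for it, and the abstract's list of visit measures does not name mindfulness.

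**The concern.** A mediation claim has two links. Arm to mindfulness is randomised. Mindfulness to outcome is not: among women in the same arm, those with higher MAAS may differ in many ways from those with lower MAAS. MAAS, SDS, SAS, the Quality of Life Index and MMAS are all self-report questionnaires. If they are answered at the same contact, mood on that day can move mediator and outcome together. Stable traits, such as a general tendency to report distress, do the same at every contact.

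Either source gives a non-zero mindfulness coefficient in the outcome model even if mindfulness changes nothing. Multiplied by a real arm effect on MAAS, it becomes an indirect effect. Because the hypothesis is primary and worded causally, the trial could report that MBSR works through mindfulness on evidence that cannot separate this from shared response variation.

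**Working it through.** **No figure to reproduce.** The article gives no effect size, path coefficient or power for the mediation model. The check therefore reads the windows side by side and then sizes the mechanism under stated assumptions.

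**Windows**

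| Item | Stated window | Where |
|---|---|---|
| Rise in mindfulness (mediator) | over the 8-week programme | Primary hypotheses |
| Outcome, primary hypothesis 1 | baseline to 8 weeks | Statistical methods; Table 1 |
| Outcome, mediation model | not stated | Statistical methods; Table 1 |
| Long-term outcome | 1 year | Secondary hypotheses |

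No passage puts the mediator before the outcome.

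**Illustration 1: no true mediation, no baseline adjustment**

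From the document: 195 per arm. Assumed: arm effects a = 0.3 SD on the mediator and c = 0.3 SD on the outcome (scored so that higher is better); zero effect of mediator on outcome; within-arm residual correlation r; both paths tested at two-sided 0.05.

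Regressing the outcome on arm and mediator gives an expected mediator coefficient of r. Hence:

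- Apparent indirect effect = a × r. At r = 0.2: 0.3 × 0.2 = 0.06.
- Apparent proportion mediated = a × r / c = 0.06 / 0.3 = 20%.
- Arm path: SE = √(2/195) = 0.101, z = 0.3/0.101 = 2.96, chance of significance Φ(2.96 − 1.96) ≈ 0.84.
- Mediator path at r = 0.2: SE ≈ √((1 − 0.04)/390) = 0.0496, z = 4.03, chance ≈ 0.98.
- Both significant: 0.84 × 0.98 ≈ 0.83.

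Simulation (2,000 runs) agrees:

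| r | Proportion apparently mediated | False mediation |
|---|---|---|
| 0 | 0% | about 5% |
| 0.1 | 10% | 42% |
| 0.2 | 20% | 84% |
| 0.3 | 30% | 85% |
| 0.4 | 40% | 85% |

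The plateau near 85% is the power of the randomised arm path.

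**Illustration 2: is baseline adjustment enough?**

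Assumed: 8-week arm effects of 0.40 SD on MAAS and −0.34 SD on SDS; overall MAAS-SDS correlation −0.4; each score half trait variance and half visit-specific state variance; no true mediation.

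- Trait and state each correlated −0.4: adjusting for both baselines multiplies the whole residual covariance matrix by 0.75, so the residual correlation stays −0.4. Indirect effect = 0.40 × −0.4 = −0.16, and 0.16/0.34 = 47% of the total. Simulated: significant in 99% of trials.
- All correlation in the trait (trait −0.8, state 0; overall 0.5 × −0.8 = −0.4): after baseline adjustment the residual covariance is −0.119 and the residual MAAS variance 0.702, a slope of −0.17. Indirect effect = 0.40 × −0.17 = −0.068, or 20% of the total. A single noisy baseline does not remove a shared trait.

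**Illustration 3: does lagging solve it?** (4-week MAAS, 8-week outcome)

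- Purely visit-specific correlation, settings of illustration 1: false mediation 4 to 5%.
- Half of the correlation carrying across visits, same settings, no adjustment for the 4-week outcome: 14%, 42%, 72% and 82% at r = 0.1, 0.2, 0.3 and 0.4.
- Adjusted for baselines and the 4-week outcome, settings of illustration 2: about 1% when trait and state are equally correlated, but about 17 to 18% with trait −0.7 and state −0.1, and 34 to 37% with trait −0.8 and state 0.
- Complete true mediation acting within the visit, no confounding: the same-visit model recovers about −0.34 and is significant in over 99% of trials. The lagged model gives 0.000 to −0.018 across runs and is significant in 1 to 3%.

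**The case against.** The strongest reply is that the article never specifies a concurrent model. Primary hypothesis 2 dates only the rise in mindfulness. The baseline-to-8-week window belongs to the ANCOVA for hypothesis 1. MAAS at 8 weeks with outcomes at 6 months is not excluded and would be ordered in time. The visits in a structural equation model are also detail that an article may leave to a full protocol or analysis plan not shown here. This stands as far as it goes: the concurrent reading is an inference, though the natural one, because later effects are placed under the secondary hypothesis with a different method.

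A reader might go further and infer that a 4-week MAAS is collected and then ignored. The documents do not support that. All subjects are reassessed at 4 weeks, but no passage says that MAAS is given then, and nothing says which visits enter the model.

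A reader might also infer that a lagged model should replace the concurrent one. Illustration 3 answers this: lagging leaves persistent confounding in place and can miss mediation that acts quickly. The choice is a trade-off.

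The reply does not remove what the article itself fixes: a causal claim at primary level, with confounder adjustment stated only for a different analysis.

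**Conclusion.** The concern holds in limited form. The article claims a causal pathway, places the mediator over the 8-week programme, fixes no order of mediator before outcome, and states no protection for the non-randomised link. On the natural, concurrent reading, a finding of mediation would say little about mechanism. Under the assumed correlations, false mediation arises in most trials once the residual correlation reaches about 0.2, and in about four in ten at 0.1. These rates depend on assumed arm effects and correlations, none of which is in the document; they show that the problem could be large, not how large it will be. The randomised comparison in primary hypothesis 1 is unaffected. The point should be settled before analysis, because it decides what primary hypothesis 2 can conclude.

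**What to change.** 1. Name the visit for the mediator and the visit for each outcome in the mediation model.
2. Adjust the structural equation model for baseline MAAS, the baseline value of the outcome and the confounders already listed for the repeated-measures analysis.
3. Add a sensitivity analysis over the residual mediator-outcome correlation, and report the correlation at which the indirect effect vanishes. Describe the result as causal only if it survives a range fixed in advance; otherwise describe it as association consistent with mediation.
4. Report a time-ordered model beside the concurrent one, not in place of it: 8-week MAAS with the 6-month outcome, which precedes the offer of MBSR to the waitlist arm, or 4-week MAAS with the 8-week outcome if MAAS is given at 4 weeks. State whether it is.

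The cost is some extra analysis and a weaker mediation claim. No new visit is needed. The limits of the time-ordered model should be stated with its result: it can miss short-acting mediation and does not remove persistent confounding.
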